**Movement Metrics:**
•**Range of Motion (ROM):** Maximum angular displacement achieved during each repetition.•**Movement Speed:** Peak and mean angular velocity during concentric and eccentric phases.•**Movement Smoothness:** Smoothness of the velocity profile quantified using spectral arc length (SPARC) and movement-unit count.•**Compensatory Movements:** Trunk motion or contralateral limb movement during unilateral exercises, used to identify compensation strategies.

**Task Completion Time:** Total time required to complete five repetitions of each exercise.

#### Secondary outcomes: subjective measures

**Perceived Exertion:** RPE score recorded after each exercise.

**Simulator Sickness:** SSQ total and subscale scores for nausea, oculomotor discomfort, and disorientation in the VR and MR groups.

**System Usability:** SUS score from 0 to 100 in the VR and MR groups, with scores above 68 indicating above-average usability [19].

#### Planned statistical analysis

Descriptive statistics will be used to summarize all objective and subjective outcomes. Continuous variables will be reported as mean ± standard deviation or median and interquartile range, depending on data distribution. For outcomes measured repeatedly across exercises and visualization modes, linear mixed-effects models will be used where appropriate, with participant included as a random effect and group, exercise, and visualization mode included as fixed effects. Model assumptions will be checked before analysis, and non-parametric alternatives will be used when required. Statistical significance will be set at (p < 0.05), with effect sizes and 95% confidence intervals reported where appropriate.

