**Positioning by muscle:**

**Anterior deltoid:** The participant sits with feet flat and trunk supported against the chair back. The arm is positioned at 90° shoulder flexion with the elbow extended and forearm neutral. The resistance band is secured at the hand/wrist and anchored to resist further shoulder flexion, and the participant pushes maximally upward.

**Middle deltoid:** The participant sits with the trunk stable. The arm is positioned at 90° abduction in the coronal plane with the elbow extended. The resistance band is secured at the hand/wrist and anchored to resist further abduction, and the participant pushes maximally outward.

**Posterior deltoid:** The participant sits with the trunk inclined forward. The arm is positioned at approximately 90° shoulder abduction/horizontal abduction with the elbow extended. The resistance band is secured at the hand/wrist and anchored to resist further horizontal abduction, and the participant pushes maximally backward.

Each muscle will be tested for 3 trials per side, resulting in 18 MVIC trials per participant. Each trial will include a 5 s maximal contraction, with 60 s rest between trials. The testing order will be fixed as anterior deltoid, middle deltoid, and posterior deltoid. The peak RMS value from the central 5 s of the highest-amplitude trial will be retained as the MVIC reference for the corresponding muscle and side. Exercise EMG will be expressed as:

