**%MVIC = (RMS_exercise / RMS_MVIC_peak) × 100**

##### Exercise familiarization and baseline trials

Following MVIC testing, participants will view a short instructional video for each standardized shoulder exercise to ensure consistent understanding of the target technique and prescribed movement range. The five exercises illustrated in Fig. 5 will be performed in the following fixed order:1.Alternating Dumbbell Front Raise2.Standing Dumbbell Shoulder Press3.Dumbbell Lateral Raise4.Bent Arm Lateral Raise5.Reverse Dumbbell Fly

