**Fig. 5 fig0005:**
[figure not shown]
Experiment exercises.

Participants will then perform five repetitions of each exercise without immersive feedback, with all EMG sensors and motion-capture markers active. These baseline trials will serve as the within-participant reference for subsequent performance comparisons. The working dumbbell load will be selected as the load with which the participant can complete all repetitions using acceptable technique, as judged by a trained research assistant using a standardized technique checklist. This load will be recorded and used for the corresponding experimental trials in Phase 4.

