### Outcome measures

#### Primary outcomes: objective measures

**Joint Angle Accuracy:** Deviation of measured shoulder joint angles, including flexion, abduction, and rotation, from the prescribed target range for each exercise. Lower deviation indicates greater movement accuracy.

**Muscle Activation Patterns:** EMG amplitude normalized to MVIC for each monitored deltoid muscle. Metrics include mean activation, peak activation, and activation timing.

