##### EMG signal processing

The following steps are applied to each EMG channel for every trial:1.**DC offset removal:** mean subtraction per channel and trial.2.**Band-pass filtering:** 4th-order zero-phase Butterworth filter, 20–450 Hz.3.**Notch filtering:** 2nd-order IIR notch filter at 50 Hz to reduce power-line interference.4.**Full-wave rectification:** absolute value of the filtered signal.5.**RMS envelope extraction:** the RMS envelope is computed using a sliding window as:$$\text{RMS}\left[n\right]=\sqrt{\frac{1}{N}\sum_{i=0}^{N-1}x^{2}\left[n-i\right]}$$where n is the current sample index, i is the sample offset within the sliding window, x is the filtered EMG signal, and N is the number of samples in the RMS window. A 50 ms RMS window is used for exercise trials for smoother visualization.

**6. MVIC normalization:** exercise EMG is expressed as a percentage of maximum voluntary isometric contraction (%MVIC) using the corresponding per-muscle, per-side MVIC reference:

$\%\text{MVIC}\left[n\right]=\frac{\text{RM}S_{\text{exercise}}\left[n\right]}{\text{RM}S_{\text{MVIC},\text{peak}}}\times \;100$where n is the current sample index, $\text{RM}S_{\text{exercise}}\left[n\right]\;$is the exercise RMS value at sample n, and $\text{RM}S_{\text{MVIC},\text{peak}}$ is the peak RMS value obtained from the central 5 s of the highest-amplitude MVIC trial.**7. Feature extraction:** mean %MVIC, peak %MVIC, time-to-peak activation, and activation duration using a 10% MVIC onset/offset threshold.

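### The stated model for %MVIC omits the baseline trials that the protocol calls the within-participant reference, so error in the MVIC denominator stays in the VR/MR/control comparison.

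*Protocol article*

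**What the plan says.** - **Outcome.** Muscle activation is a primary outcome: "EMG amplitude normalized to MVIC for each monitored deltoid muscle", summarised as mean, peak and timing (Primary outcomes: objective measures).
- **Formula.** The percentage is defined as "MVIC = (RMS_exercise / RMS_MVIC_peak) × 100", and the offline pipeline computes it "using the corresponding per-muscle, per-side MVIC reference" (EMG signal processing). Each participant therefore has six denominators.
- **Denominator.** "Each muscle will be tested for 3 trials per side, resulting in 18 MVIC trials per participant". The reference is the peak RMS of the highest-amplitude trial. No reliability figure is given.
- **Baseline.** Five repetitions of each exercise are recorded without immersive feedback: "These baseline trials will serve as the within-participant reference for subsequent performance comparisons" (Exercise familiarization and baseline trials).
- **Model.** "For outcomes measured repeatedly across exercises and visualization modes, linear mixed-effects models will be used where appropriate". The fixed effects listed are group, exercise and mode; the one random effect is for participant. No baseline, channel or participant-by-exercise term is named, and no response scale.
- **Fallback.** "Model assumptions will be checked before analysis, and non-parametric alternatives will be used when required".

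**The concern.** The procedures and the analysis section do not meet. One gives the baseline trials the role of reference for performance comparisons. The other lists the model terms and leaves baseline out.

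This matters most for %MVIC because of how it is built. If a participant's reference for a channel is wrong by a factor, every baseline and trial value on that channel is wrong by the same factor. In VR versus MR versus control, the error differs between people, and a participant random effect does not remove it. It becomes part of the between-participant variance against which the group effect is tested. Randomisation keeps the comparison unbiased, so what is at stake is precision, on a primary outcome. The recorded baseline carries the same error and could remove most of it.

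Two smaller points follow from the same structure. One participant effect cannot represent six separate references if channels are pooled. Without a participant-by-exercise term, stable differences in how a person performs a given exercise go into the residual used to test visualization mode.

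**Working it through.** The article states no power, precision or sample-size figure, so there is nothing to reproduce.

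**Step 1: algebra.** For one participant and channel, let U be the exercise RMS, B the baseline RMS, M the true reference and e the error factor in the recorded reference.

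- Recorded values: 100·U/(M·e) and 100·B/(M·e).
- Raw difference: 100·(U − B)/(M·e). It is still scaled by 1/e.
- Log difference: log U − log B. Both M and e cancel.

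Illustration with assumed values: a true baseline of 40 %MVIC, a trial value of 44 and a reference 30% too high. The recorded values are 40/1.3 = 30.8 and 44/1.3 = 33.8. The difference falls from 4 to 4/1.3 = 3.1 points, while the ratio stays 1.10.

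**Step 2: group comparison by hand, log scale.** Assumptions: 20 per arm; true between-participant CV 30%; reference-error CV 30%; participant-by-exercise CV 15%; residual CV 15%; 5 exercises, 3 blocks and one baseline; group ratio 1.10; two-sided 5%. Log variances are ln(1.09) = 0.0862 for a 30% CV and ln(1.0225) = 0.0223 for a 15% CV.

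- Without baseline: SD of a participant mean = √(2×0.0862 + 0.0223/5 + 0.0223/15) = 0.422. SE = 0.422×√(2/20) = 0.134. ln(1.10)/SE = 0.0953/0.134 = 0.71. Power = Φ(0.71 − 1.96) ≈ 0.11.
- As log ratio to baseline: SD = √(0.0223/5 + 0.0223/15) = 0.077. SE = 0.0244. 0.0953/0.0244 = 3.91. Power = Φ(3.91 − 1.96) ≈ 0.97.

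**Step 3: simulation** (2,000 runs per setting, two arms, same CVs, 20 per arm, assumed exercise levels of 20, 30, 40, 50 and 60 %MVIC; mode effect 5%, group effect 10%).

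| Contrast | Reference-error CV | Raw | Log |
|---|---|---|---|
| Group, no baseline | 0 | 0.15 | 0.16 |
| Group, no baseline | 30% | 0.10 | 0.11 |
| Group, baseline covariate | 0 | 0.93 | 0.96 |
| Group, baseline covariate | 30% | 0.90 | 0.97 |
| Mode, participant effect only | 0 | 0.48 | 0.71 |
| Mode, participant effect only | 30% | 0.36 | 0.73 |
| Mode, plus participant-by-exercise | 0 | 0.82 | 0.90 |
| Mode, plus participant-by-exercise | 30% | 0.80 | 0.91 |

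Other sample sizes, group contrast at 30% error: without baseline, power is 0.09 on both scales at 12 per arm, and 0.12 (raw) and 0.14 (log) at 30 per arm. With the baseline covariate it is 0.69 (raw) and 0.82 (log) at 12, and 0.98 and above 0.99 at 30.

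If all exercises sit at 40 %MVIC, the mode contrast with only a participant effect gives 0.65 raw against 0.72 log with no reference error, and 0.64 against 0.75 at 30%.

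Under no effect, the mode test with only a participant effect rejected in 0.002 to 0.009 of runs, well below 5%. With the participant-by-exercise term it rejected in 0.051 to 0.055.

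**Step 4: how far the baseline gain depends on assumptions.** Step 2 implies a correlation of about 0.98 between baseline and trial means: shared variance 0.1768, divided by √(0.1813×0.1783). With covariate adjustment the SD is 0.422×√(1 − ρ²). At assumed ρ = 0.95, 0.9 and 0.8 the SD is 0.132, 0.184 and 0.253, and power by the same formula is 0.63, 0.37 and 0.22, against 0.11 without baseline.

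**Step 5: counter-check with additive effects and noise** (20 per arm; mode effect 3%, group effect 10%). For the mode contrast with a participant effect only, raw and log power are 0.44 and 0.27 with no reference error, 0.38 and 0.26 at 15%, and 0.27 and 0.26 at 30%. For the group contrast at 30% error, the baseline covariate lifts power from 0.13 to 0.95 raw and from 0.16 to 0.88 log.

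**The case against.** The strongest reply is that this is a condensed article and the analysis plan is not shown. Response scale, transformation and detailed random effects are commonly left to that plan, and the article does promise an assumption check. On scale, that reply stands. A reader might infer that %MVIC will be modelled raw, but the article names no scale, so its silence is not an error.

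The reply does not dispose of the baseline point. The article lists the model terms and elsewhere assigns the baseline trials a role that the list does not honour.

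Other limits also stand:

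- A reader might infer that the five exercises differ widely in activation. No level is given for any of them, and the log advantage for mode contrasts is modest if levels are equal.
- A reader might infer that a log scale costs nothing. It changes the estimand to a ratio of geometric means and loses power if effects and noise are additive (Step 5).
- Much of the simulated loss in the mode contrast comes from the missing participant-by-exercise term. Adding it on the raw scale lifts power from 0.36 to 0.80 at 30% error.
- Log transformation alone does almost nothing for the group comparison (0.10 against 0.11). Baseline does the work.

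**Conclusion.** The point holds as a matter of precision and internal consistency. The model as listed omits the reference that the protocol itself designates, and for %MVIC this leaves error in the MVIC denominator in the group comparison on either scale. No bias or inflated type I error is shown.

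Under the stated assumptions, using baseline raises power for a 10% group effect from about 0.10 to 0.90 (raw) or 0.97 (log) at 20 per arm. The direction also holds when effects are additive. The size depends on assumed sample size, CVs and activation levels, and on a very high baseline-to-trial correlation, none of which the document gives. At a correlation of 0.8 the gain is only from 0.11 to 0.22.

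The log scale is a sensible secondary choice for a ratio outcome, not a correction of something stated wrongly.

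Two wider readings are not supported. The EMG results would not become independent of MVIC quality: activation duration uses a 10% MVIC threshold, so the timing and duration metrics are not helped, and the displayed feedback is itself scaled by the reference (Stage C of the runtime pipeline). The argument also does not extend to task completion time or angular velocity, which have no MVIC denominator.

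**What to change.** In the Planned statistical analysis, for mean and peak %MVIC:

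1. Include the baseline value of the same exercise and channel as a covariate in the VR/MR/control comparison.
2. Analyse both metrics, and their baseline, on the log scale. The reference error cancels exactly in the log ratio to baseline. With a covariate it cancels to the extent that the fitted slope is near 1.
3. Fit each muscle and side separately, or add a participant-by-channel term.
4. Add a participant-by-exercise term.
5. Report group and mode effects as ratios with 95% confidence intervals, and give raw-scale results as a sensitivity analysis.

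The cost is a few sentences and no new data, since the baseline trials are already scheduled. The downside is that effects are read as ratios of geometric means and some power is lost if effects and noise are truly additive. Fixing the scale before data collection also prevents a choice of scale after seeing the results.

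### Every objective outcome is labelled primary (7 named, up to 31–37 variables) at a single p < 0.05 with no lead outcome or contrast, which puts the familywise error well above 5%

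*Protocol article*

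**What the plan says.** *Outcome measures* opens with the heading "Primary outcomes: objective measures" and lists seven outcomes before the subjective secondary ones begin: joint-angle accuracy, muscle activation, range of motion, speed, smoothness, compensatory movement and task completion time. None is singled out.

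Several of the seven are composite:

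- Joint-angle accuracy: "Deviation of measured shoulder joint angles, including flexion, abduction, and rotation, from the prescribed target range for each exercise".
- Muscle activation: "EMG amplitude normalized to MVIC for each monitored deltoid muscle. Metrics include mean activation, peak activation, and activation timing". *EMG signal processing* extracts a slightly different set: "mean %MVIC, peak %MVIC, time-to-peak activation, and activation duration using a 10% MVIC onset/offset threshold".
- Speed: "Peak and mean angular velocity during concentric and eccentric phases".
- Smoothness has two metrics. *Kinematic processing* gives compensation two.

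*Study design* describes two group comparisons, VR against MR and the immersive groups against control, and a within-participant comparison of three visualization modes. It does not say which matters most. *Planned statistical analysis* proposes mixed models with group, exercise and visualization mode as fixed effects, and sets the level: "Statistical significance will be set at (p < 0.05". It mentions neither a hierarchy nor an adjustment. The specifications table says that the trial is not registered.

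**The concern.** A primary label tells the reader that a significant result carries the stated error rate. That works if one outcome and one comparison bear the label, or if a rule shares the 5% among several. Here a whole class bears it, no comparison leads, and the only rule is the common threshold. A significant result on any one of the measures, for any of the comparisons, could be reported as a primary finding, and its 5% would not describe the chance that the study produces such a finding by accident. *Protocol validation* says that group-level testing and conclusions on delivery and visualization mode await the complete sample, so inference is intended and not only description.

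**Working it through.** The article states no familywise error rate, so there is no figure to reproduce. The check counts the primary variables and then computes the error rate for a range of readings.

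**Count**

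| Outcome | Variables | Source |
|---|---|---|
| Joint-angle accuracy | 3 (flexion, abduction, rotation) | Primary outcomes |
| EMG | 6 channels × 3 metrics = 18, or 6 × 4 features = 24 | EMG electrode placement; Primary outcomes; EMG signal processing |
| Range of motion | 1 | Movement Metrics |
| Speed | 2 × 2 = 4 | Movement Metrics |
| Smoothness | 2 | Movement Metrics |
| Compensation | 2 | Kinematic processing |
| Completion time | 1 | Primary outcomes |

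- EMG metrics from the outcome section: 3 + 18 + 1 + 4 + 2 + 2 + 1 = 31.
- EMG features from the processing section: 3 + 24 + 1 + 4 + 2 + 2 + 1 = 37.
- Muscle and side handled inside one model: 3 + 3 + 1 + 4 + 2 + 2 + 1 = 16, or 17 with four features.
- One variable per named outcome: 7.

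**Assumptions.** No true effects, two-sided tests (sidedness is not stated), and the same correlation ρ between every pair of variables. The article gives no correlations, so ρ runs from 0 to 0.9. The two group contrasts are orthogonal because the groups are to be of equal size.

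**Formulas**

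- Independent tests: FWER = 1 − 0.95^m. For example, 1 − 0.95^7 = 30.2%, 1 − 0.95^14 = 51.2%, 1 − 0.95^37 = 85.0%, 1 − 0.95^74 = 97.8%.
- Correlated tests, k variables, one contrast: F = 1 − E[a(U)^k], where U is standard normal and a(u) = Φ((1.96 − √ρ·u)/√(1−ρ)) − Φ((−1.96 − √ρ·u)/√(1−ρ)).
- Two orthogonal contrasts: 1 − (1 − F)². For 37 variables at ρ = 0.9, F = 0.181 and 1 − 0.819² = 0.329.

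**Chance of at least one false-positive primary result (%)**

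| Variables | Contrasts | ρ = 0 | 0.3 | 0.5 | 0.7 | 0.9 |
|---|---|---|---|---|---|---|
| 7 | 1 | 30.2 | 27.1 | 23.0 | 17.8 | 11.4 |
| 7 | 2 | 51.2 | 46.9 | 40.6 | 32.5 | 21.5 |
| 16 | 1 | 56.0 | 47.6 | 37.4 | 26.4 | 14.6 |
| 16 | 2 | 80.6 | 72.5 | 60.8 | 45.8 | 27.1 |
| 31 | 1 | 79.6 | 67.1 | 51.4 | 34.3 | 17.4 |
| 31 | 2 | 95.8 | 89.2 | 76.4 | 56.8 | 31.7 |
| 37 | 1 | 85.0 | 72.3 | 55.4 | 36.5 | 18.1 |
| 37 | 2 | 97.8 | 92.3 | 80.1 | 59.7 | 32.9 |

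If the three pairwise mode contrasts are tested as well (an assumption, as the article does not specify pairwise tests), simulation with 40,000 draws at ρ = 0.5 gives 69% for 7 variables and 97% for 37.

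**After the change proposed below.** With one outcome and two orthogonal contrasts, Holm tests the smaller p-value at 0.05/2 = 0.025. With no true effects the familywise rate is 1 − 0.975² = 4.9%.

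**The case against.** Four points can be made for the article.

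1. **The analysis plan is not shown.** Adjustment methods and the list of tests commonly sit there, and the article is silent on adjustment; it does not rule it out. This stands for the mechanics. It does not cover the choice of primary outcome, which is protocol content and is made here for the whole objective class. An analysis plan that named one primary outcome would contradict the article.

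2. **37 is the upper reading.** A reader might infer that 37 variables are each tested for several contrasts. The article lists no individual tests. Its outcome section names three EMG metrics, not four, and muscle and side could be terms in one model. The pilot work uses one main angle per exercise. This stands, and the count has to be given as a range from 7 to 37.

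3. **A false-positive primary result is not shown to be almost certain.** A reader might reach that from 37 × 3 = 111 independent tests, for which 1 − 0.95^111 = 99.7%. That needs independence, no true effect anywhere and several contrasts per variable. Range of motion, angular velocity, completion time and the EMG features come from the same repetitions and are likely to be correlated. This stands too.

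4. **The absence of a stated direction of benefit for EMG amplitude and speed is not an error if tests are two-sided.** Agreed. It matters only when choosing which outcome should lead.

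The article also promises effect sizes and confidence intervals, and this is a single-session laboratory study in healthy adults. Both lower the stakes, but neither gives the primary label a defined error rate.

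**Conclusion.** The concern holds as a fault in labelling and ranking. The objective class as a whole is primary, no outcome or comparison leads, and one 0.05 threshold covers everything. The error rate exceeds 5% in every case computed, and the smallest value is more than double the nominal level. The size depends on two things that the article does not settle: how many variables become separate tests, and how strongly they are correlated. The result should therefore be given as the range in the table and not as one percentage. All figures assume no true effects and equal pairwise correlation; they describe the plan if followed as written, with no adjustment added elsewhere.

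**What to change.** Before full data collection, state the following in the outcome and analysis sections:

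- **One primary outcome.** Joint-angle accuracy in the main plane of each exercise is a natural candidate: it is listed first, its better direction is stated, and the pilot already assigns flexion to Exercises 1–2 and abduction to Exercises 3–5. The choice is the sponsor's.
- **Two primary contrasts on that outcome,** both already in *Study design*: VR against MR, and the mean of VR and MR against control, with Holm adjustment at 0.05.
- **A key secondary family:** the three pairwise visualization-mode contrasts on the same outcome within the immersive groups, with Holm adjustment. The 5% then applies within each family, not across the two, and the text should say so.
- **All other objective measures** as secondary or exploratory, with false-discovery-rate control or with intervals and no confirmatory claims.

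No measurement is dropped and no procedure changes. The text edit is small, but choosing the lead outcome is a scientific decision. The price is that fewer outcomes can be reported as significant primary results.
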